### Interventions

#### Experimental intervention

Temporary fracture fixation with fixateur externe and secondary reamed intramedullary nailing not earlier than 48 hours after trauma.

#### Control intervention

Primary reamed nailing of the femoral shaft fracture.

Early treatment will be performed, depending on the result of randomization, within 24 h (early) with definitive internal stabilization (control intervention) or in two separate procedures with primary temporary fixation (fixateur externe) and definitive internal stabilization at a later time point (experimental intervention).

The second procedure may not be initiated before 48 hours after trauma unless there are urgent medical reasons demanding early management. These reasons must be documented.

Thus, as soon as the patient stabilizes with ventilation, coagulation, hemodynamics, and the metabolic system secondary surgery can be performed (but not earlier than 48 hours after trauma).

The following criteria are defined as a sign of patient stabilization:

1. Ventilation - paO2/FiO2 > 200 (if ventilated) or no need for ventilation

2. Coagulation - prothrombin time > 60% and platelets > 60,000/μl

3. Hemodynamics - no need for Noradrenalin or Adrenalin and MAP > 60 mmHg

4. Metabolic system - BE >-6.0 mmol/l

Furthermore, none of the signs listed below of systemic or local inflammation should be present:

Temperature > 38.5°C

White blood cell count > 20,000/μl or < 4,000/μl

Local pin infection

### Control/Comparators

The chosen control regimen (primary reamed nailing) is currently as well established in routine care as the experimental intervention (temporary fracture fixation with fixateur externe and secondary reamed nailing not earlier than 48 hours after trauma). As discussed above, so far there is no evidence that one of the treatment regimens is superior to the other [4,5].

### Method of assigning patients to treatment groups

All multiple trauma patients with femur shaft fractures and age > or = 18 years that present to the involved hospitals will be recorded and eligibility will be checked. The probability of death will be calculated on the trial website using clinical data as described below. If all inclusion criteria are fulfilled the patient will be randomized and documentation will be started (figure 1). Reasons for non-inclusions must be recorded. Allocation concealment will be guaranteed by internet randomization where patients have to be named before allocation to one of the therapy arms. The validated system for internet randomization will be provided by the Coordinating Center for Clinical Studies Cologne (KKSK). This system generates the allocation sequence as follows: The randomisation sequence is blocked using varying block sizes between 6 and 10. Furthermore, randomisation is stratified by study center, in order to adjust for center-specific variation in treatment routines.

**Figure 1 F1:**
[figure not shown]
**Frequency and scope of study visits: Simplified visit plan**. R = Recruitment and Randomisation; Fix. ex. = Fixateur externe; F/U = Follow-Up; Data marked with an asterisk (*) will be collected only if they are available from routine measurements.

### Calculation of probability of death

The probability of death will be calculated according to the following formula of Rixen et al. [23,24]:

With:

BE - Base Excess (mmol/l)

Quick - Prothrombin time (%)

Age - Age of patient

GCS - Glasgow Coma Scale

ISS - Injury Severity Score

This calculation can be done by entering the five variables at the trial website just before randomization. The individual probability of death is visible to the investigator.

### Other baseline characteristics

The pattern and severity of injuries will be documented in detail. For each body region the AIS (abbreviated injury scale) will be used to quantify injury severity. This allows to calculate standard prognostic scores, such as the ISS and the New ISS. In addition the TRISS score will be used to describe injury severity. A fourth more recent score will also be used to describe the severity of trauma. This score, the revised injury severity classification (RISC) score, includes nine variables and has been shown to have very good prognostic capacity. However, as the RISC requires more variables (some of which may not be available in the emergency room quickly), this score will only be used for explorative adjustment of analyses.

In addition to these variables, standard demographic parameters (gender, body mass index, etc.), further physiologic variables (heart rate, temperature, etc.), routine laboratory results on admission (hemoglobin, leukocytes, creatinine, etc.), comorbidities (liver cirrhosis, immunosuppression, renal insufficiency, acute myocardial infarction, etc.) and medical management before randomisation (volume loading in the field and in the emergency room, need for thoracic drainage, radiographs done on admission, etc.) will be recorded.

### Prior and Concomitant Therapy

All concomitant surgical and non-surgical therapy is allowed and key aspects (ventilation, surgery etc.) will be recorded.

### Outcome measures

#### Primary efficacy endpoint

Primary endpoint is the reduction of organ failure as measured by the maximum SOFA score within 28 days after trauma.

The SOFA score has been developed for the sequential evaluation and description of organ failure and has been shown to be a suitable indicator of prognosis in trauma patients [29]. For the present trial, the 5 item SOFA score (exluding CNS) will be used. The central nervous system (CNS) will be excluded due to the known problems in receiving valid data from patients who were intubated and ventilated. Thus the maximum SOFA score will be 20 points (4 points for each organ).

The SOFA score will be assessed daily for the first 28 days after trauma (figure 1). Documentation will start on ICU and will be continued until the patient is returned to a normal ward, where the SOFA score will be set to zero. If the patient is discharged home within the first 28 days, SOFA score is set to zero by definition. If the patient is transferred to another hospital, the last observation will be continued until day 28. Patients who died during the first 28 days after trauma will be assigned the maximum possible SOFA score (20 points) for each day after death.

From the daily assessment of SOFA score, the worst value within the first 28 days will be used as primary endpoint. This corresponds to the intuitive mechanism of reducing the "second hit" which is induced by the operative trauma.

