### Eligibility

#### Inclusion criteria

• Multiple trauma (injury of at least two body regions)

• Injury severity score (ISS) ≥ 16

• Femoral shaft fracture which can be treated in principle by nail or fixateur externe

• Beginning of surgical treatment within 24 hours after trauma

• Patient aged 18 years and older

• Calculated probability of death between 20% and 60% [23,24]

• All factors known which are needed for the calculation of probability of death [age, ISS, Glasgow Coma Scale (GCS), base excess (BE), prothrombin time]

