#### Secondary endpoints

• Hospital mortality

• Cumulative organ failure = sum of SOFA score points for the first 28 days

• Incidence of Acute Respiratory Distress Syndrome (ARDS)

• Incidence of Systemic Inflammatory Response Syndrome (SIRS) and sepsis during ICU stay

• Quantity and duration of surgical interventions, anaesthetics, and costs of surgery (material, time)

• Length of ICU stay

• Length of hospital stay

• Number of ventilator-free days

• Therapeutic Intervention Scoring System (TISS) 28 during ICU stay

• Rate of phlegmona of the medullary cavity

• Rate in which conversion to internal fixation was not possible (DCO group only)

• Rate of pseudarthrosis

• Functional outcome at discharge, 6 and 12 months after trauma

• Quality of life at 6 and 12 months after trauma (determined by POLO chart [30])

• Glasgow Outcome Scale (GOS) at discharge, 6 and 12 months after trauma

• Return to work

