### Proposed sample size/Power calculations

The primary hypothesis is that the damage control principle is able to reduce the extent of organ failure. Organ failure is measured daily by the SOFA score (five organs, excluding CNS, 0-4 points per organ). The maximum SOFA score during ICU stay is used as primary outcome measure. It is assumed that the maximum SOFA score could be reduced by 1-2 points. This corresponds to a reduction from "organ failure" to "organ dysfunction", or from "organ dysfunction" to "normal organ function" for one organ. Data from Ferreira et al. indicate that a 2 point increase in SOFA score correlates with an average 10% increase in mortality [29]. According to the database of the Deutsche Interdisziplinäre Vereinigung Intensivmedizin (DIVI; quality assessment in intensive care; 45.000 admissions 2000-2004) maximum SOFA score is about 3.2 ± 3.2 in a general ICU population, and 3.3 ± 3.1 in emergency admissions with trauma. Thus the estimated effect (1.5 points reduction) corresponds to a standardized effect size of 0.5. Assuming usual error rates (a = 0.05; b = 0.20), 64 patients per group would be required. However, due to the non-normal nature of the distribution and the use of non-parametric statistics, the number of patients to be randomized has to be increased by 10%. Thus, the total sample size is set to 140 patients (70 per group). Compliance and rate of loss to follow-up do not affect primary outcome measures.

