## Discussion

Today, there is a trend towards the concept of "Damage Control Orthopedics" in the management of multiple trauma patients with long bone fractures. But, evidence from the current literature is insufficient. As discussed above, results are contradictory, a generalized management strategy is missing. Thus, in the era of "evidence-based medicine", there is the need for a more specific, clarifying randomized controlled trial. Therefore this new trial was initiated.

To our knowledge, this trial is the first to evaluate the risk adapted damage control orthopedic surgery of femur shaft fracutres in multiple trauma patients in a randomized controlled design. In 2003, Pape et al. [32] presented their results of a randomized controlled trial. They investigated the impact of intramedullary instrumentation versus damage control for femoral fractures on immunoinflammatory parameters and complications [32,33]. But, in contrast to this study, where a risk adaption is performed, they excluded multiple trauma patients with severe brain and thoracic injuries (AIS > 3) and patients in unstable or critical condition, too. In summary, the included patients were injured less severely. Furthermore, Pape et al. did not define criteria that must be fulfilled for performing the secondary definitive procedure. Therefore these two trials are not comparable in the authors' opinion.

Since there is still no clear evidence for the superiority of one of the strategies participation in the trial is not associated with an increased risk by itself. If one of the strategies proves superiority the benefit (reducing the organ failure) is evident. The main endpoint is a surrogate endpoint for mortality, i. e. the trial may lead to a definite treatment strategy in patients with multiple trauma lowering the overall mortality. If non-inferiority of the primary internal fixation can be proven, it can be assumed that hospital stay, number of operations etc. are lower in this group, thus lowering the expenses.

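### Both SOFA endpoints score death as 20, so the primary is a composite of death and organ failure and should be named and interpreted as one

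*Protocol article*

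**What the plan says.** The primary endpoint section defines the outcome as organ failure: "Primary endpoint is the reduction of organ failure as measured by the maximum SOFA score within 28 days after trauma". The score has five items of 0 to 4 points, without the CNS item, so it runs from 0 to 20. From the daily scores, "the worst value within the first 28 days will be used as primary endpoint". Deaths enter by rule: "Patients who died during the first 28 days after trauma will be assigned the maximum possible SOFA score (20 points) for each day after death".

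The one other SOFA endpoint is secondary: "Cumulative organ failure = sum of SOFA score points for the first 28 days". It adds up the same daily scores and so carries the same 20s.

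The inclusion criteria select for risk of death: "Calculated probability of death between 20% and 60" percent.

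The sample size section frames the trial's claim in terms of organ failure: "The primary hypothesis is that the damage control principle is able to reduce the extent of organ failure". It explains the 1 to 2 point target as one organ moving by one category of function. The Discussion says that if one strategy proves superior, its benefit, meaning less organ failure, is evident. It also says: "The main endpoint is a surrogate endpoint for mortality". Later the Discussion explains that giving deaths the maximum value was intended.

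**The concern.** A patient who dies within the window, with at least one scored day after death, has a maximum SOFA of 20 whatever organ function was recorded before. In a population chosen for a substantial risk of death, many patients may get their value from this rule and not from a measurement. The label and the stated conclusion do not allow for that.

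Two misreadings follow. A difference made by deaths alone would be reported as reduced organ failure. A real improvement in organ function among survivors could be diluted by deaths that do not differ between arms, and a null result would then be read as no effect on organ failure.

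The surrogate statement has a related fault. A surrogate stands in for an outcome that it does not contain. Here death is a component, so part of any agreement between the endpoint and mortality is built in.

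**Working it through.** **1. The plan's own figure.** With a standardized effect of 0.5, two-sided alpha 0.05 and 80% power, the t-test needs 63.8, so 64 per group. Then 64 × 1.10 = 70.4, so 70 per group. The stated 64 and 140 in total reproduce.

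**2. What decides the U-test.** The test compares every patient in one arm with every patient in the other. With 28-day mortality m in both arms, both patients survive in (1−m)² of pairs, exactly one dies in 2m(1−m), and both die (tied at 20) in m².

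| m | both survive | one dies | both die |
|---|---|---|---|
| 10% | 81% | 18% | 1% |
| 20% | 64% | 32% | 4% |
| 40% | 36% | 48% | 16% |
| 60% | 16% | 48% | 36% |

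Only the first column compares observed organ failure in both patients.

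**3. Share of variance due to death status.** Let survivors have mean μ and SD s, and deaths score 20. Total variance is (1−m)s² + m(1−m)(20−μ)², and the second term is the part due to death status. The documents give no survivor distribution, so two assumptions bracket it: 3.3 ± 3.1 (the sample size section's figure for emergency trauma admissions) and 8 ± 3.5.

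- m = 40%, 3.3 ± 3.1: 66.9 / (5.8 + 66.9) = 92%.
- m = 40%, 8 ± 3.5: 34.6 / (7.35 + 34.6) = 82%.
- Over m = 20 to 60%: 85 to 95% under the first assumption, 70 to 88% under the second.
- At m = 10%: 74% and 54%.

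**4. A shift made by deaths alone.** With identical survivors, a mean difference of 1.5 points needs a mortality difference of 1.5/(20−μ): 1.5/16.7 = 9.0 percentage points at μ = 3.3, and 1.5/12 = 12.5 points at μ = 8.

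**5. Simulated U-test.** 70 per arm, significance level 0.048, skewed (gamma) survivor scores with assumed SD 3, rounded and capped to 0–20, at least 4,000 runs per setting.

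Survivor benefit of 1.5 points (mean 8 to 6.5), equal mortality in both arms:

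| mortality | power |
|---|---|
| 0% | 87% |
| 10% | 69% |
| 20% | about 49% |
| 30% | 32% |
| 40% | 20% |
| 60% | about 8% |

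Identical survivors (mean 8), mortality difference only:

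| mortality | significant | mean difference |
|---|---|---|
| 40% v 35% | 8% | 0.6 |
| 40% v 27.5% | 25% | 1.5 |
| 40% v 20% | about 54% | 2.4 |

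**6. The 28-day sum.** A death on day 3 leaves 25 later days at 20 points, or 500 of a possible 28 × 20 = 560. This endpoint cannot serve as a check on the primary.

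**The case against.** The scoring is deliberate, disclosed in the Discussion, and in line with an objective that names both morbidity and mortality. Giving death the worst rank and using a U-test is an accepted answer to truncation by death, since it stops an early death from passing as a low maximum SOFA. This stands, and it is why the scoring should not change.

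A reader might infer that the plan has no endpoint for organ failure at all. The documents do not support that. ARDS incidence is listed and measures respiratory failure without the 20-point rule, and SIRS and sepsis, ventilator-free days and TISS-28 cover related morbidity. Hospital mortality is a separate secondary endpoint, and predicted and observed survival are compared within each group at the interim and final analyses. Deaths will therefore be visible. These secondary endpoints are exploratory, however, and none gives multi-organ severity apart from death.

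A reader might also infer that deaths from head injury invalidate a score without a CNS item. They do not. The item was dropped because valid data cannot be obtained in ventilated patients, and under randomisation deaths unrelated to fixation cost power but do not bias the comparison.

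Nor is a positive result produced by deaths alone the likely outcome. The Discussion's figure of about 1300 per arm for a mortality trial is in the range for a difference of about 5 points (for example 30% v 25% needs 1251 per arm at 80% power), and a difference of that size was significant in only 8% of simulated trials. Some deaths will also reflect multi-organ failure, so pairs decided by death are not all irrelevant to the hypothesis.

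Finally, component analyses may be set out in an analysis plan that is not shown. Their absence from the article is not the fault. The fault is the label, the conclusion and the surrogate claim that the article itself states.

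**Conclusion.** The point holds as one of labelling and interpretation. Neither SOFA-based endpoint separates organ failure from death, and in the selected population the primary contrast is largely a mortality contrast: death status carries about 70 to 95% of the variance at 20 to 60% mortality. A 1.5-point survivor benefit that would have about 87% power without deaths has about 20% at 40% mortality. A significant result does not by itself make less organ failure evident, a null result does not rule it out, and the endpoint is not a surrogate for mortality.

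The sizes rest on two assumptions that the documents do not settle: that observed 28-day mortality is near the predicted risk, and that survivor scores are as stated in the working. The effect is smaller but still sizeable at 10% mortality (54 to 74% of variance, 69% power). Nothing here shows the primary comparison to be biased or the test to be invalid.

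**What to change.** Keep the 20-point rule for deaths and the U-test.

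- In the primary endpoint section, the sample size section and the Discussion, call the primary endpoint a composite of death and organ failure.
- In the Discussion, replace the surrogate statement with a description of the endpoint as a composite that includes mortality, and withdraw the statement that superiority makes a reduction in organ failure evident.
- Report two supportive components beside the primary: 28-day mortality, which matches the SOFA window, and the maximum SOFA actually observed, both in survivors and in all patients up to death or day 28.
- Attribute a positive result to organ failure, mortality or both in the light of these components.

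The observed-score analysis should not become a formal condition for the conclusion. Patients who die early have few scored days and can show low maxima, so a strategy that keeps very sick patients alive could look worse on it. It has to be read with the mortality result, and that is the small downside.

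The cost is wording and two supportive summaries from daily scores already collected. The primary test and the sample size are not altered by this change.

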#### Secondary endpoints

• Hospital mortality

• Cumulative organ failure = sum of SOFA score points for the first 28 days

• Incidence of Acute Respiratory Distress Syndrome (ARDS)

• Incidence of Systemic Inflammatory Response Syndrome (SIRS) and sepsis during ICU stay

• Quantity and duration of surgical interventions, anaesthetics, and costs of surgery (material, time)

• Length of ICU stay

• Length of hospital stay

• Number of ventilator-free days

• Therapeutic Intervention Scoring System (TISS) 28 during ICU stay

• Rate of phlegmona of the medullary cavity

• Rate in which conversion to internal fixation was not possible (DCO group only)

• Rate of pseudarthrosis

• Functional outcome at discharge, 6 and 12 months after trauma

• Quality of life at 6 and 12 months after trauma (determined by POLO chart [30])

• Glasgow Outcome Scale (GOS) at discharge, 6 and 12 months after trauma

• Return to work

### Adverse events

All adverse events (AE) during hospital stay will be documented for both study groups. Rate of serious adverse events (SAE), e.g. mortality or ARDS incidence, are part of the secondary endpoints and will be monitored closely. Serious adverse events will be reported to the Principle Coordinating Investigator as soon as possible, at the latest within 24 hours.

Possible complications of the risk-adaptive treatment („damage control orthopedics”, DCO):

Since there are at least two interventions in this treatment arm, there is a hypothetical higher risk of infection in these patients, longer ventilation time, and a certain rate of patients in whom no change from fixateur externe to intramedullary nail is possible and thus, resulting in a higher rate of pseudarthrosis, worse functional result, delayed weight bearing and lower quality of life.

Complications of the primary definitive treatment are primarily the hypothetically higher mortality, increase in duration and rate of SIRS, sepsis and/or multi organ failure (MOF).

Expected Adverse Events

Complications of surgery include:

• Infection

• Delayed healing

• Bleeding

• Nerve injury

• Tendon and muscle injury

• Thrombosis/embolism

• Pseudarthrosis

• Compartment syndrome

### Proposed sample size/Power calculations

The primary hypothesis is that the damage control principle is able to reduce the extent of organ failure. Organ failure is measured daily by the SOFA score (five organs, excluding CNS, 0-4 points per organ). The maximum SOFA score during ICU stay is used as primary outcome measure. It is assumed that the maximum SOFA score could be reduced by 1-2 points. This corresponds to a reduction from "organ failure" to "organ dysfunction", or from "organ dysfunction" to "normal organ function" for one organ. Data from Ferreira et al. indicate that a 2 point increase in SOFA score correlates with an average 10% increase in mortality [29]. According to the database of the Deutsche Interdisziplinäre Vereinigung Intensivmedizin (DIVI; quality assessment in intensive care; 45.000 admissions 2000-2004) maximum SOFA score is about 3.2 ± 3.2 in a general ICU population, and 3.3 ± 3.1 in emergency admissions with trauma. Thus the estimated effect (1.5 points reduction) corresponds to a standardized effect size of 0.5. Assuming usual error rates (a = 0.05; b = 0.20), 64 patients per group would be required. However, due to the non-normal nature of the distribution and the use of non-parametric statistics, the number of patients to be randomized has to be increased by 10%. Thus, the total sample size is set to 140 patients (70 per group). Compliance and rate of loss to follow-up do not affect primary outcome measures.

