Although mortality would have been the most appreciated endpoint, a trial with mortality as the main endpoint would need approximately 1300 patients per arm. In addition to the fact that such a trial is almost undoable for practical reasons the concentration on mortality does not cover all aspects of the planned intervention since the damage control approach primarily tries to limit the sequelae of the "second hit" by surgical intervention. This is reflected by the measurement of organ failure by appointing maximum values for patients who died. The SOFA score has been developed for the sequential evaluation and description of organ failure and has been shown to be a suitable indicator of prognosis in trauma patients [29].

A significant effect may only be shown in a group of medium probability of death (20-60%), especially concerning maximum SOFA-score, as the type of procedure chosen in patient groups of very high or very low mortality will most likely have only a minimal effect on this endpoint.

Because the most important factors that determine prognosis in multiple trauma patients are considered, a comparison of this heterogenic patient collective is possible.

In the current literature, another facet of the optimal surgical treatment in multiple trauma patients is discussed: Biochemical/immunologic factors. It has been shown that the traumatic tissue damage stimulates a maximal activation of the immune system, which leads to its depletion and debilitation [34-36]. As a consequence of a failing immune system a systemic inflammatory response syndrome (SIRS) or sepsis can occur. Both are potentially life threatening complications, in the course of which all organ systems can be affected [34,37,38].

Some of the best analyzed pro-inflammatory cytokines are tumor necrosis factor (TNF)-α [39,40], and the interleukines (IL)-6 and IL-8 [41-43]. Circulating IL-6 is quickly detectable after trauma [42] and has been shown to correlate with trauma load [44].

But so far, the transfer of results into clinical context and the verification for potential decision making (therapy) with respect to risk reduction during secondary surgical procedures after trauma failed.

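### The planning SD of about 3 ignores that deaths are scored 20 in patients with 20-60% predicted mortality, so the stated 80% power is unsupported

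*Protocol article*

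**What the plan says.** All references are to the protocol article.

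- **Endpoint** (Primary efficacy endpoint): "Primary endpoint is the reduction of organ failure as measured by the maximum SOFA score within 28 days after trauma". It is a five-organ score from 0 to 20, and the worst daily value counts.
- **Deaths** (same section): patients who die in the first 28 days "will be assigned the maximum possible SOFA score (20 points) for each day after death". Because the worst value counts, such a death becomes a 20. The Discussion presents this as deliberate: "This is reflected by the measurement of organ failure by appointing maximum values for patients who died".
- **Population** (Inclusion criteria): "Calculated probability of death between 20% and 60" per cent.
- **Planning data** (Proposed sample size/Power calculations): "maximum SOFA score is about 3.2 ± 3.2 in a general ICU population", and "3.3 ± 3.1 in emergency admissions with trauma".
- **Conversion** (same section): "Thus the estimated effect (1.5 points reduction) corresponds to a standardized effect size of 0.5". Then: "Assuming usual error rates (a = 0.05; b = 0.20), 64 patients per group would be required". A 10% increase for non-normality and the non-parametric test gives 70 per group.
- **Test** (Statistical analyses): a U-test, with a final significance level of 0.048 after one interim look.

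**The concern.** The SD behind the standardized effect comes from broad registry groups. Neither group is restricted to the trial's risk band, and neither can contain many patients scored 20. The trial's own outcome is a mixture: survivors spread over the lower part of the scale, and a large block of deaths tied at the top. The sample-size paragraph carries neither the risk criterion nor the death rule into its SD. The 10% uplift is its only adjustment to the distribution.

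What is at stake is the power claim for the primary hypothesis. The Discussion already looks ahead to showing non-inferiority of primary nailing. Readers who believe the trial had 80% power for 1.5 points would read too much into a non-significant result.

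**Working it through.** **1. The plan's own figure.** A standardized effect of 0.5 for 1.5 points implies an SD of 3.0. With two-sided alpha 0.05 and 80% power, the t-test solution is 63.8, so 64 per group. Then 64 × 1.1 = 70.4, in line with 70 per group and 140 in total. The arithmetic reproduces; the question is the SD that goes in. (The quoted SDs give 1.5/3.1 = 0.48 and 1.5/3.2 = 0.47. That rounding is minor.)

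**2. Can the planning figures describe this endpoint?** With 20% deaths scored 20, the deaths alone add 0.20 × 20 = 4 points to the mean, already above 3.3. More generally, a variable with mean 3.3 and SD 3.1 can have at most this share at 20:

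p ≤ 3.1² / (16.7² + 3.1²) = 9.61 / 288.5 = 3.3%.

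Conversely, take 20% deaths and no spread at all among survivors. An SD of 3.1 then needs √(0.2 × 0.8) × (20 − m) = 3.1, so 20 − m = 7.75 and the survivor mean m is 12.25. Any spread among survivors pushes it higher. Neither step uses outside data.

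**3. The SD under the trial's scoring rule.** For a share p of deaths at 20, and survivors with mean m and SD s:

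SD = √[(1 − p)s² + p(1 − p)(20 − m)²].

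For example, p = 0.2, m = 3.3, s = 3.1: √(0.8 × 9.61 + 0.16 × 278.89) = √52.31 = 7.23. The survivor mean of 3.3 is the document's registry figure. Means of 6 to 10 are assumptions for sicker survivors; s = 3.1 throughout.

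| Survivor mean | SD, 20% deaths | SD, 40% | SD, 60% | Multiple of 3.1 |
|---|---|---|---|---|
| 3.3 | 7.23 | 8.53 | 8.41 | 2.33-2.75 |
| 6 | 6.25 | 7.27 | 7.13 | 2.02-2.34 |
| 8 | 5.54 | 6.35 | 6.20 | 1.79-2.05 |
| 10 | 4.87 | 5.46 | 5.28 | 1.57-1.76 |

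**4. Power of the planned test.** The U-test is rank-based, so the SD does not settle its power. It was simulated with 70 per arm, alpha 0.048, survivors drawn from a rounded gamma distribution and deaths set to 20. For a 1.5-point shift in survivors with equal mortality in both arms:

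| Deaths in each arm | Survivors 3.3 ± 3.1 | Survivors 8 ± 3.1 |
|---|---|---|
| 0% | 94% | 82% |
| 10% | 79% | 65% |
| 20% | 57% | 45% |
| 40% | 23% | 19% |
| 60% | 9% | 7% |

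Repeated runs give roughly 44-57% at 20% deaths and 16-22% at 40%. The zero-deaths row shows that 70 per group does what the plan says when nobody is scored 20; the loss comes from the deaths tied at the top.

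Other forms of a 1.5-point effect:

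- The whole-group mean falls by 1.5 only through fewer deaths: about 14-39%.
- A proportional effect in survivors lowers the whole-group mean by 1.5: about 44-79% over 20-40% deaths.
- A 1.5-point survivor shift plus a 5-point mortality reduction: 20% versus 15% deaths gives 81% (survivors 3.3 ± 3.1) or 70% (8 ± 3.1), with a total mean difference of about 1.9. At 40% versus 35% it gives 47% or 39%, with a total difference of about 1.6.

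**The case against.** Four arguments can be made for the plan.

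*The U-test does not depend on the SD.* This stands. A reader might put the inflated SD into the two-means formula, get about 17-44% power at 70 per group, and conclude that the trial is very unlikely to detect its target. The documents do not support that, because those are figures for a test the trial does not use. The rank-test simulations give higher power in several scenarios, up to about 79% for a proportional survivor effect.

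*The treatment may also lower mortality.* The sample-size section ties SOFA points to mortality, and the Discussion calls the endpoint a surrogate for it. A 5-point reduction is close to what the quoted 1300 per arm for a mortality endpoint implies: 30% versus 25% needs 1251, and 35% versus 30% needs 1377. This helps near 20% mortality, but the total difference then exceeds the planned 1.5 points.

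*20-60% is predicted, not observed, mortality.* True, and the plan itself compares the two. At 10% actual deaths, power is 79% with mildly ill survivors and 65% with survivors at 8 ± 3.1. The protocol nevertheless chose its population for that predicted risk.

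*The shape of the survivor distribution matters.* With survivors as mildly ill as the registry average, a different assumed shape gave 81% at 20% deaths, but 39% at 40%.

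These arguments identify favourable corners. They do not restore 80% across the protocol's own range.

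**Conclusion.** The concern holds as a fault in an input, not in the arithmetic: 64 and 140 follow from the figures used. The planning SD cannot describe an outcome in which far more than 3% of patients are expected to score 20, and the stated 80% power is therefore unsupported. For a 1.5-point effect the planned U-test gives roughly 44-57% at 20% deaths and 16-22% at 40% (survivor shift, equal mortality), about 14-39% (through deaths only), or about 44-79% (proportional survivor effect, 20-40% deaths). About 80% needs mortality near or below 20% with mildly ill survivors, or an added mortality reduction that takes the total difference above 1.5 points.

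A reader might also infer that the SD at least nearly doubles. That goes too far: the multiple is about 1.6 to 2.75, and it depends on a survivor mean that the documents do not give for this population. The power figures rest on assumed survivor distributions and on observed mortality resembling the predicted range. The mismatch itself rests only on the protocol's own numbers.

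**What to change.** In the sample-size section:

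1. State whether the 1.5 points apply to survivors or to the whole group with deaths scored 20.
2. State a survivor distribution and a 28-day mortality for each arm, with their source, for patients who meet the 20-60% criterion.
3. Simulate the U-test on that distribution with 70 per arm at 0.048, over a plausible range of mortality.
4. Replace the 80% claim with the resulting power and the effect that 140 patients can detect with this test.

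The work is a short simulation and a rewritten paragraph. The price is a less favourable stated power. Correcting the statement needs no extra patients, but it does not cure low power: if the sponsor wants to keep 80% for 1.5 points, the sample size has to be derived again from the same inputs.
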